## Abstract

**Background:**

Elbow dislocations can be classified as simple or complex. Simple dislocations are characterized by the absence of fractures, while complex dislocations are associated with fractures of the radial head, olecranon, or coronoid process. The majority of patients with these complex dislocations are treated with open reduction and internal fixation (ORIF), or arthroplasty in case of a non-reconstructable radial head fracture. If the elbow joint remains unstable after fracture fixation, a hinged elbow fixator can be applied. The fixator provides stability to the elbow joint, and allows for early mobilization. The latter may be important for preventing stiffness of the joint. The aim of this study is to determine the effect of early mobilization with a hinged external elbow fixator on clinical outcome in patients with complex elbow dislocations with residual instability following fracture fixation.

**Methods/Design:**

The design of the study will be a multicenter prospective cohort study of 30 patients who have sustained a complex elbow dislocation and are treated with a hinged elbow fixator following fracture fixation because of residual instability. Early active motion exercises within the limits of pain will be started immediately after surgery under supervision of a physical therapist. Outcome will be evaluated at regular intervals over the subsequent 12 months. The primary outcome is the *Quick *Disabilities of the Arm, Shoulder, and Hand score. The secondary outcome measures are the Mayo Elbow Performance Index, Oxford Elbow Score, pain level at both sides, range of motion of the elbow joint at both sides, radiographic healing of the fractures and formation of periarticular ossifications, rate of secondary interventions and complications, and health-related quality of life (Short-Form 36).

**Discussion:**

The outcome of this study will yield quantitative data on the functional outcome in patients with a complex elbow dislocation and who are treated with ORIF and additional stabilization with a hinged elbow fixator.

**Trial Registration:**

The trial is registered at the Netherlands Trial Register (NTR1996).

## Background

The elbow joint is the second most commonly dislocated joint in adults. The annual incidence of elbow dislocations in children and adults is 6.1 per 100,000 [1]. Elbow dislocations are classified as being simple or complex [2]. Simple dislocations are dislocations without fractures. Complex dislocations are associated with fractures of the radial head, olecranon, or coronoid process. In patients with an elbow dislocation the incidence of radial head fractures is 36%, whereas coronoid process fractures occur in 13%, and olecranon fractures in four percent of patients [1].

The radial head and coronoid process are considered to be important bony stabilizers of the elbow. The fundamental goal in the management of complex elbow dislocations is the restoration of the osseous-articular restraints. Therefore, the majority of these complex dislocations is treated with open reduction and internal fixation (ORIF) [3] or primary arthroplasty in case of a non-reconstructable radial head fracture.

Assessment of stability of the joint following ORIF of a complex elbow dislocation is essential. Signs of instability are redislocation, a positive pivot shift test and positive valgus and varus stress testing. At present instability following ORIF or arthroplasty is usually treated with primary ligament repair and/or a period of plaster immobilization.

A period of plaster immobilization may result in a limited range of motion and a stiff elbow with subsequent disability. A hinged external elbow fixator, on the other hand, may provide enough stability to start early mobilization after ORIF or arthroplasty and may prevent residual instability and stiffness [4,5]. No randomized controlled trials comparing hinged external fixation and plaster immobilization are available. This may be due to the low incidence of patients with a complex elbow dislocation with remaining instability after ORIF or arthroplasty. Until now only small observational studies of patients with complex elbow dislocations have been published [2,3,5-12]. These studies showed promising functional results following treatment with a hinged elbow fixator [11,12].

The primary objective of this prospective cohort study is to study the functional outcome, pain, and health-related quality of life in patients who sustained a complex elbow dislocation and were treated with ORIF and/or arthroplasty of the radial head and a hinged external fixator due to residual instability. Our hypothesis is that early mobilization will prevent stiffness and will result in a satisfactory functional outcome at one year.

## Methods/Design

### Study design

Multi-center cohort study in all consecutive patients who sustained a complex elbow dislocation and were treated with a hinged external fixator for residual instability after ORIF and/or arthroplasty of the radial head. Sixteen centers in the Netherlands will participate. The study started August 28, 2009.

### Recruitment and consent

The decision to apply the hinged fixator for residual instability following fracture fixation will be left to the discretion of the surgeon. If a fixator is applied, patients will receive information and a consent form from the attending physician, the clinical investigator or a research assistant postoperatively. Patients meeting all inclusion criteria and none of the exclusion criteria will be included before discharge or at the time of their first outpatient visit (two weeks after surgery), which will give them on average one week to consider their participation.

### Study population

Patients meeting the following inclusion criteria are eligible for enrolment:

1. Men or women aged 18 years and older (with no upper age limit)

2. Patient with a complex elbow dislocation (i.e., dislocation of the elbow joint, combined with at least a fracture of the radial head, coronoid process, or olecranon)

3. Patient was treated with a hinged external fixator after ORIF and/or arthroplasty of the radial head due to persistent instability

4. Provision of informed consent by patient

Since there is currently no consensus regarding the most valid and reliable test for assessing elbow joint instability, this will be left to the discretion of the surgeon performing the operation. This reflects common practice, and will increase translatability of the outcome of our study. In order to warrant performance of stability tests across participating sites, a detailed description of stability tests (*i.e*., varus stability, valgus stability, and pivot shift test for posterolateral rotatory stability) is included in the protocol.

If any of the following criteria applies, patients will be excluded:

1. Patients with a concomitant distal humeral fracture

2. Patients with additional substantial traumatic injuries of the affected upper limb

3. Patients who underwent repair of the collateral ligaments

4. Patients with an impaired elbow function (i.e., stiff or painful elbow or neurological disorder of the upper limb) prior to the injury

5. Retained hardware around the affected elbow

6. Likely problems, in the judgment of the investigators, with maintaining follow-up (e.g., patients with no fixed address will be excluded)

7. Insufficient comprehension of the Dutch language to understand the rehabilitation program and other treatment information in the judgment of the attending physician

Exclusion of a patient because of enrolment in another ongoing drug or surgical intervention trial will be left to the discretion of the attending surgeon on a case-by-case basis.

### Intervention

The external fixator used is the Orthofix^® ^Elbow Fixator (Orthofix Verona, Italy). The surgical approach to the fracture site is left to the surgeon's discretion. Following ORIF of the fractures and/or arthroplasty of the radial head, the center of rotation of the elbow is identified. A two mm K-wire is inserted into the center point of the capitellum humeri which is identified on an exact lateral fluoroscopic image. Next, the external fixator is mounted, first fixating the proximal humeral clamp and subsequently the distal ulnar clamp. Exact reduction of the elbow joint is evaluated with image intensifier in lateral and anteroposterior direction during flexion and extension. The surgical technique is described in more details elsewhere [13]. After surgery, patients are allowed to use a sling for two days to one week. Pin-site care will be performed daily by the patient following instruction given by the treating physician. After surgery patients will receive indomethacin 2dd 50 mg for six weeks (in combination with acid blocking medication) in order to prevent heterotopic ossification of the elbow, unless NSAIDs are contraindicated [14]. The external fixator will be removed six weeks after surgery. Extension, flexion and pro- and supination active and passive exercises are started immediately after surgery if tolerated under supervision of a professional physical therapist, who they can freely select.

### Outcome measures

The primary outcome measure is the *Quick-*DASH (Disabilities of the Arm, Shoulder and Hand) score, which reflects both function and pain after one year [15]. The DASH Outcome Measure is a validated 30-item, self-reported questionnaire designed to help describe the disability experienced by people with upper-limb disorders and also to monitor changes in symptoms and function over time [15,16].

The *Quick-*DASH is a shortened version of the DASH Outcome Measure. Instead of 30 items, the Quick-DASH uses 11 items (scored 1-5) to measure physical function and symptoms in people with any or multiple musculoskeletal disorders of the upper limb. The right and left elbow will be assessed separately. At least 10 of the 11 items must be completed for a score to be calculated. The scores will be transformed to a 0-100 scale for easy comparison. A higher score indicates greater disability. The test-retest reliability of the *Quick*-DASH was 0.90 [17].

Like the DASH, the *Quick-*DASH also has two optional modules intended to measure symptoms and function in athletes, performing artists and other workers whose jobs require a high degree of physical performance. These optional models are scored separately; each contains four items, scored 1-5. All items must be completed for a score to be calculated.

The secondary outcome measures are:

• Functional outcome (Mayo Elbow Performance Index and Oxford Elbow Score)

• Pain level at both sides (VAS)

• Range of Motion of the elbow joint at both sides

• Radiographic healing of the fractures

• Rate of secondary interventions

• Rate of complications

• Health-related quality of life (SF-36)

The Mayo Elbow Performance Index (MEPI) is one of the most commonly used physician-based elbow rating systems. This index consists of five parts: pain (with a maximum score of 45 points), ulnohumeral motion (20 points), stability (ten points), the ability to perform five functional tasks (5 × 5 points) and the patient response. If the total score is between 90 and 100 points, it is considered excellent; between 75 and 89 points, good; between 60 and 74 points, fair; and less than 60 points, poor [18].

The Oxford Elbow Score is a 12-item questionnaire. It is comprised of three one-dimensional domains: elbow function, pain and social-psychological, with each domain comprising of four items with good measurement properties [19]. This is a validated questionnaire in the UK and was translated to Dutch by the proper translation procedure, which uses the technique of translation and back-translation [20-22]. Permission for translation and the use of the Oxford Elbow Score for this study was obtained from Oxford and Isis Outcomes, part of Isis Innovation Limited (website: http://www.isis-innovation.com/)

Pain level will be determined using a 10-point Visual Analog Scale (VAS), in which zero implies no pain and ten implies the worst possible pain.

Range of motion (ROM) will be determined by measure flexion/extension and pro-/supination on both sides using a goniometer.

Radiographic healing will be determined using X-rays. Fractures are considered healed if one of the following three criteria is met: (a) Bridging of fracture by callus/bone trabeculae or osseous bone; (b) Obliteration of fracture line/cortical continuity; (c) Bridging of fracture at three cortices.

Secondary intervention within one year of initial treatment to promote fracture healing, relieve pain, treat infection, or improve function will be recorded. This includes incision and drainage for surgical site infection or deep infection, repositioning or removal of the fixator, reosteosynthesis, implant removal, or ligament repair.

Complications within one year of initial treatment will be recorded. These include heterotopic ossification, infections, bleeding, venous thrombosis, and neurological deficits)

The Short-Form 36 (SF-36) is a validated multi-purpose, short-form health survey with 36 questions that represent eight health domains that are combined into a physical and a mental component scale [23]. The Physical Component Scale (PCS) combines the health domains of physical functioning (PF; ten items), role limitations due to physical health (RP; four items), bodily pain (BP; two items), and general health perceptions (GH; five items). The Mental Component Scale (MCS) combines the health domains of vitality, energy, or fatigue (VT; four items), social functioning (SF; two items), role limitations due to emotional problems (RE; three items), and general mental health (MH; five items). Scores ranging from zero to 100 points are derived for each domain, with lower scores indicating poorer function. These scores will be converted to a norm-based score and compared with the norms for the general population of the United States (1998), in which each scale was scored to have the same average (50 points) and the same standard deviation (ten points).

In addition to the outcome variables mentioned above, the following data will be collected:

1. Intrinsic variables (baseline data): age, gender, American Society of Anesthesiologists' ASA classification, tobacco consumption, alcohol consumption, comorbidity, dominant side, medication use, *Quick-*DASH score prior to the injury, pain level at both sides prior to the injury (VAS), and SF-36 score prior to the injury.

2. Injury related variables: affected side, mechanism of injury, and postoperative assessment of varus, valgus and posterolateral rotatory instability, fracture location (*i.e*., radial head, coronoid process, olecranon), fracture classification of the coronoid process according to Regan & Morrey [24], and fracture classification of the radial head according to Mason & Johnston [25].

3. Intervention-related variables: surgical delay (*i.e*., time between fracture and surgery), time between injury and start of physical therapy, and number of physical therapy sessions

### Study procedures [Table 1]

**Table 1 T1:** Schedule of events

	Screening	Enrolment	Baseline	< 48 h post-surgery	2 weeks (7-28 d)	6 weeks (4-8 we)	3 months (11-15 we)	6 months (5-7 mo)	12 months (12-14 mo)
**Screening**	**X**								

**X-ray**	**X**			**X**	**X**	**X**	**X**	**X**	**X**

**Informed Consent**		**X**							

**Baseline data**			**X**						

***Quick-*DASH**			**X**			**X**	**X**	**X**	**X**

**Pain (VAS)**			**X**		**X**	**X**	**X**	**X**	**X**

**SF-36**			**X**			**X**	**X**	**X**	**X**

**Clinical follow-up**					**X**	**X**	**X**	**X**	**X**

**Revision surgery**					**X**	**X**	**X**	**X**	**X**

**Complications**					**X**	**X**	**X**	**X**	**X**

**ROM**					**X**	**X**	**X**	**X**	**X**

**MEPI**						**X**	**X**	**X**	**X**

**Oxford Elbow Score**						**X**	**X**	**X**	**X**

**Early withdrawal**				*	*	*	*	*	*

*, only if applicable

Clinical assessments will take place at the time of admission to the hospital (baseline), two weeks (7-28 days window), six weeks (4-8 weeks window), three months (11-15 weeks window), six months (5-7 months window), and 12 months (12-14 months window) after surgery. At each follow-up moment, the research coordinator or research assistant will ascertain patient status (*i.e*., secondary interventions, adverse events/complications), and will verify information within medical records. At the last visit, the surgeon will document any surgery that may be planned for the patient.

Anteroposterior and lateral X-rays of the elbow will be made at the time of presentation to the hospital (baseline), within 48 hours post surgery, and at all follow-up visits listed above. These X-rays will be used to determine the time to radiographic healing and amount and location of heterotopic ossification.

At baseline, patients will be asked to complete the *Quick-*DASH, VAS, and SF-36 questionnaires. This relates to the situation prior to the injury, so in order to minimize recall bias as much as possible, the questionnaires will be completed as soon after surgery as possible. At the two weeks follow-up visit and each visit thereafter, the range of motion of the elbow joint will be measured by a doctor or research assistant using a goniometer. At these follow-up visits, the patients will complete a questionnaire relating to pain (VAS). The MEPI index will be determined from six weeks onwards. At the six week follow-up visit and each visit thereafter patients will be asked to complete the *Quick-*DASH, Oxford Elbow Score, and SF-36 questionnaires.

### Sample size calculation

Calculation of the required sample size for this study is not constructive. This study is a case series based on the assumption that for introducing and acquiring experience in a new operative technique a sample size of 30 patients is required [26,27].

### Statistical analysis

Data will be analyzed using the PASW Statistics version 18.0.1 or higher (SPSS, Chicago, Illinois, USA). Normality of continuous data will be checked by inspecting the frequency distributions (histograms) and normal Q-Q plots. Data will be reported in compliance with the CONSORT (CONsolidation of Standards of Reporting Trials) guidelines [28,29]. In the unlikely event that a fixator will be removed within six weeks, patients will be followed and analyzed on an intention to treat basis.

Descriptive analysis will be performed in order to report baseline characteristics (*i.e*., intrinsic, injury-related and fracture-related variables) and outcome measures. For continuous variables (*e.g*., age, *Quick-*DASH score, MEPI, VAS, and SF-36 score) mean ± SD (if normally distributed) or medians and percentiles (if not normally distributed) will be calculated. For categorical variables (*e.g*., gender, ASA grade, alcohol and tobacco consumption, dominant and affected side) frequencies will be calculated.

Multiple linear regression analysis will be performed in order to model the relation between different covariates and the *Quick-*DASH score. Intrinsic and fracture-related variables will be added as covariate. Similar models will be made to model the relation between covariates and the other outcome measures. A p-value < 0.05 will be taken as the threshold of statistical significance.

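### The planned regressions put 14 or more covariates, from a set left open, on 30 patients and repeat this across the outcomes at p < 0.05

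*Protocol article*

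**What the plan says.** The Sample size calculation section makes no calculation: "Calculation of the required sample size for this study is not constructive". It adopts the assumption that, to gain experience with a new operative technique, "a sample size of 30 patients is required".

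The Statistical analysis section puts description first and then plans a multiple linear regression of the Quick-DASH. On covariates it says "Intrinsic and fracture-related variables will be added as covariate". On the remaining outcomes it says "Similar models will be made to model the relation between covariates and the other outcome measures". On testing it says "A p-value < 0.05 will be taken as the threshold of statistical significance". The section gives no cap on covariates, no selection step, no adjustment for multiple testing and no exploratory label.

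The variables are listed at the end of the Outcome measures section in three groups: intrinsic, injury-related and intervention-related. The intrinsic group holds "age, gender, American Society of Anesthesiologists' ASA classification, tobacco consumption, alcohol consumption, comorbidity, dominant side, medication use", then the pre-injury Quick-DASH, then "pain level at both sides prior to the injury (VAS), and SF-36 score prior to the injury". Fracture location and the two fracture classifications sit inside the injury-related group. The intervention-related group holds surgical delay, "time between injury and start of physical therapy, and number of physical therapy sessions".

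**The concern.** The covariate sentence is a rule, and that rule does not fit the stated sample size. Thirty was chosen for experience with a technique, not for the precision of a regression. With about two patients per covariate, a model fits well whether or not any covariate matters, and real associations are easily missed. Repeating it over every outcome at an unadjusted 0.05 adds chance findings.

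The set itself is also open. No listed group is called fracture-related, so what enters the model could be settled after the data are seen.

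Finally, the only model named is linear, while the outcomes it is extended to include complications and secondary interventions, which are not continuous.

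The Discussion section says the data may serve the design of later randomized trials. Inflated R-squared values and unstable prognostic factors could carry over into those designs.

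**Working it through.** The plan's own figure is n = 30. It cannot be reproduced, because no effect size, standard deviation or power is given.

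**Covariate count (Outcome measures section)**
- Intrinsic items: 8 in the first part of the list, plus pre-injury Quick-DASH, VAS and SF-36 = 11.
- Narrow reading of fracture-related: location, coronoid class, radial head class = 3. Total 11 + 3 = 14.
- Splitting VAS by side (+1), SF-36 into its physical and mental components (+1) and location into three indicators (+2): 14 + 4 = 18 coefficients, with one term for each graded item.
- Wide reading, all injury-related items: affected side, mechanism, three instability assessments and the 3 fracture items = 8. Total 11 + 8 = 19.
- If fracture-related is a slip for intervention-related: 11 + 3 = 14 again.

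**Outcome count**
- Nine named measures: Quick-DASH, MEPI, Oxford Elbow Score, VAS, range of motion, radiographic healing, secondary interventions, complications, SF-36.
- Twelve if, for example, VAS is split by side, range of motion into its two arcs and SF-36 into two components: 9 + 3 = 12.

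**Formulas** (n patients, p covariates)
- Residual df = n − p − 1.
- Expected R-squared with no association = p/(n − 1).
- Expected chance findings with no association anywhere = 0.05 × p × number of models.

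| p (n = 30) | Patients per covariate | Residual df | Expected null R-squared |
|---|---|---|---|
| 3 | 10.0 | 26 | 3/29 = 0.10 |
| 14 | 2.1 | 15 | 14/29 = 0.48 |
| 18 | 1.7 | 11 | 18/29 = 0.62 |
| 19 | 1.6 | 10 | 19/29 = 0.66 |

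Chance findings: 0.05 × 14 × 9 = 6.3, and 0.05 × 18 × 12 = 10.8.

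**Power and precision**, by simulation (4,000 runs, independent normal covariates entered together, two-sided tests at 0.05). Two-sidedness and the effect sizes are assumptions; the article gives neither.

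| p (n = 30) | Power, partial R-squared 0.10 | 0.20 | 0.30 | 95% CI width at 0.20 (residual SDs) |
|---|---|---|---|---|
| 3 | 0.39 | 0.68 | 0.89 | 0.81 |
| 14 | 0.24 | 0.46 | 0.65 | 1.10 |
| 18 | 0.18 | 0.37 | 0.51 | 1.34 |

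The interval is 1.10/0.81 = 1.36 times as wide with 14 covariates as with 3, and 1.34/0.81 = 1.65 times as wide with 18. With pure noise, about 41% of models with 14 or 18 covariates show at least one p < 0.05, against 14% with 3.

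**Sensitivity to loss.** If 10% of patients are lost (assumed, n = 27), 14 covariates leave 12 df with a null R-squared of 14/26 = 0.54, and 18 leave 8 df with 18/26 = 0.69. Power at partial R-squared 0.20 falls to 0.37 and 0.26.

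**The case against.** The strongest reply is that the study calls itself a case series. Its main yield is descriptive, and that result stands whatever the regressions do. A separate analysis plan, not shown, may contain a selection step or an exploratory label. Both points have force and lower the severity. They do not remove the problem: the article states what will be entered, and the plain reading is that all of it goes in.

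Four stronger readings are tempting, and the documents do not support them.

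- *The output will be mostly noise.* Each least-squares test keeps its 5% error rate however many covariates there are. The false share of significant results depends on how many covariates truly matter. If two do, at partial R-squared 0.20, it is 12 × 0.05/(12 × 0.05 + 2 × 0.46) = 0.39 with 14 covariates, and 16 × 0.05/(16 × 0.05 + 2 × 0.37) = 0.52 with 18. Over partial R-squared 0.10 to 0.30 it runs from about 0.32 to 0.69, and it falls if more covariates are real.
- *At least 18 covariates.* Eighteen results from splitting choices that the article does not make; the narrow count is 14. Higher counts from dummy coding need numbers of categories that the article does not give.
- *The model leaves out early mobilization.* The descriptive sentence in the Statistical analysis section lists fracture-related third, after intrinsic and injury-related, where the variable list has intervention-related. It may be a mislabel, in which case therapy timing is included. Even so, it would not answer the question: exercises start straight after surgery if tolerated, and there is no comparison group.
- *Linear models are invalid for rare events.* No event rates are given. Healing is not simply yes/no either, since Study procedures speaks of time to healing, and 'similar' could allow another model type. What stands is that only linear regression is named.

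**Conclusion.** The concern holds in a limited form. On every reading of the variable list (14, 18 or 19 terms), 30 patients cannot support the regression as described. The firm consequences are an expected null R-squared of 0.48 to 0.66, 10 to 15 residual degrees of freedom, wide intervals, low power, and some 6 to 11 chance findings if nothing is related to anything. The covariate set is not pinned down, and the named model does not suit every outcome it is extended to.

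The degrees of freedom and null R-squared rest on the article's own n and variable list, with all covariates entered together. The chance-finding range also depends on counting 9 or 12 outcomes. The power figures rest on assumed effects and two-sided tests.

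This should be fixed. It is not critical, because the descriptive report of the Quick-DASH at one year does not depend on it.

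**What to change.** Replace the covariate sentence in the Statistical analysis section, and the two sentences after it, along these lines:

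- Model the 12-month Quick-DASH on at most two or three covariates, chosen by the sponsor and named before analysis. In choosing, note that patients with impaired elbow function before the injury are excluded, so the pre-injury Quick-DASH may vary little.
- Align the term fracture-related with the groups in the Outcome measures section, so that each candidate variable belongs to one named group.
- Report coefficients with 95% confidence intervals, labelled exploratory, without a significance threshold.
- Use the same small model for continuous secondary outcomes only.
- Report yes/no outcomes as counts with exact 95% confidence intervals.
- State that the regression cannot estimate the effect of early mobilization in this single cohort.

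The cost is wording only; no new data are needed. The downside is that fewer exploratory associations are examined.

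### "Similar models" carries a regression with about 14 to 18 covariates over to yes/no outcomes in 30 patients, where neither a linear nor a logistic version can be supported

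*Protocol article*

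**What the plan says.** All places are in the protocol article.

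- **Model (Statistical analysis).** One model is named: "Multiple linear regression analysis will be performed in order to model the relation between different covariates and the" Quick-DASH score. The covariate rule is "Intrinsic and fracture-related variables will be added as covariate", with no selection rule and no maximum. The next sentence extends this to everything else: "Similar models will be made to model the relation between covariates and the other outcome measures". The significance threshold is p < 0.05.
- **Summaries (Statistical analysis).** The descriptive analysis covers baseline characteristics and outcome measures. Continuous variables get a mean and SD "if normally distributed) or medians and percentiles (if not normally distributed) will be calculated". Categorical variables also have a rule, and its list of examples ends with "dominant and affected side) frequencies will be calculated".
- **Outcomes (Outcome measures).** The secondary list puts fracture healing, the rate of secondary interventions and the rate of complications beside the continuous scores. Healing is a met/not-met state: "Fractures are considered healed if one of the following three criteria is met". The other two are events recorded within one year.
- **Time to healing (Study procedures).** "These X-rays will be used to determine the time to radiographic healing and amount and location of heterotopic ossification". After the postoperative film, X-rays are taken at 2 weeks, 6 weeks, and 3, 6 and 12 months. The secondary list gives healing no time element.
- **Size (Sample size calculation).** 30 patients, set by assumption.

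**The concern.** The extending sentence makes no exception, and no other type of model is named. An analyst who follows the text would fit a multiple linear model with the whole covariate list to outcomes that take only two values. An analyst who reads the sentence more freely would fit a logistic model with the same list. Either way, the number of terms is large against 30 patients and larger than any plausible number of events.

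At stake are the covariate associations for complications, secondary interventions and healing. They would come from models that give impossible risks or have no finite estimate, and would be read against p < 0.05. The Discussion says the data may be used to design later trials, so such associations could be taken further than they deserve.

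Time to healing raises a related but conditional question. It is a time known only to lie between two visits, and the only stated rule for a continuous quantity is a mean or a median with percentiles.

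**Working it through.** The protocol gives no calculated figure to reproduce. Event rates and healing times are not stated, so they are assumptions shown as ranges.

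**1. Number of covariates** (from the variable lists under Outcome measures)
- Intrinsic: age, gender, ASA class, tobacco, alcohol, comorbidity, dominant side, medication, and pre-injury Quick-DASH, pain and SF-36 = 11.
- Fracture-related: location, coronoid classification, radial head classification = 3.
- Minimum: 11 + 3 = 14 terms.
- With pain entered per side (+1), SF-36 as two component scores (+1) and location as three indicators (+2): 14 + 4 = 18. Multi-level classes would add more.

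**2. Events available.** Events = 30 × rate.
- 10%: 3 events; 20%: 6; 30%: 9.
- Events per covariate run from 3/18 = 0.17 to 9/14 = 0.64.
- For healing, the same holds if the rarer state (healed or not healed) has a share of 10-30%.

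**3. Simulated fits.** n = 30, independent normal covariates unrelated to the outcome, 2,000 data sets per setting (separation checked on 1,000). Data sets with no event were left out.

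| Covariates | Event rate | Linear: fitted risks outside 0-1 | Linear: type I error, one covariate | Logistic: completely separated |
|---|---|---|---|---|
| 14 | 10% | 33% | 5.2% | 98% |
| 14 | 20% | 25% | 4.8% | 86% |
| 14 | 30% | 20% | 4.7% | 70% |
| 18 | 10% | 36% | 4.9% | 100% |
| 18 | 20% | 30% | 5.4% | 99% |
| 18 | 30% | 26% | 5.0% | 97% |

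At least 99% of the linear fits contained one or more impossible risks. With fewer covariates the problem shrinks but remains: 6.6-19.4% of fitted risks lie outside 0-1 with 5 covariates, and 0.7-4.8% with one. Complete separation means that the maximum-likelihood logistic estimates do not exist.

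**4. What a count with an exact interval gives** (Clopper-Pearson, 95%)
- 3/30 = 10% (2.1% to 26.5%)
- 6/30 = 20% (7.7% to 38.6%)
- 9/30 = 30% (14.7% to 49.4%)

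**5. Time to healing, if healing is dated at the first visit that shows it.** Assumed Weibull times (shape 2) and visits at 2, 6, 13, 26 and 52 weeks:

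| True median (weeks) | True mean | Mean of first-healed visits | Late by |
|---|---|---|---|
| 8 | 8.5 | 12.7 | 4.2 |
| 10 | 10.6 | 15.6 | 5.0 |
| 12 | 12.8 | 18.6 | 5.8 |
| 16 | 17.0 | 24.7 | 7.7 |
| 20 | 21.3 | 30.1 | 8.8 |

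The median of such dates falls on a visit: 13 weeks in the first three rows and 26 weeks in the last two. A fracture not healed at the last film has no date to enter.

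**The case against.** **Similar need not mean linear.** The word can be read as analogous models suited to each outcome, with details in a full protocol or SAP not shown. That is a fair reading of the word. It does not rescue the plan, because the covariate list is stated here, and the logistic model that this reading implies is separated in most data sets.

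**Yes/no outcomes already have a valid summary.** This stands. A reader might infer that the plan offers only means, medians and linear regression. It does not: frequencies are specified for categorical variables, and the descriptive analysis covers the outcomes.

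**The p-values are not shown to be wrong.** This also stands. A reader might infer from impossible fitted risks that the tests are invalid. In the simulations, the type I error for a single covariate stayed near 5%. These were null simulations with normal covariates, so they show only that there is no gross failure under the null. The case rests on an unsuitable and overfitted model, not on false p-values.

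**The healing bias is conditional.** A reader might infer that unhealed patients will be dropped, or that the first healed visit will be taken as the exact date. The protocol says neither, and it lists healing as an outcome without a time. What remains is that Study procedures sets a time to healing, that this time is observed only at visits, and that a mean or median of visit dates would be late if that dating were used.

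**Replaced radial heads.** Inclusion covers patients treated "after ORIF and/or arthroplasty of the radial head due to persistent instability", so a reader might infer that prostheses distort the healing denominator. The outcome is worded per fracture, and nothing says that a replaced head is counted. This is silence, not an error.

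**Conclusion.** The point holds in limited form. The article extends its only named model, with about 14 to 18 covariates, to yes/no outcomes in 30 patients. Neither the linear nor the logistic reading gives a supportable multivariable model: roughly 20-36% of fitted risks are impossible under the first, and about 70-100% of data sets are completely separated under the second. These figures rest on assumed event rates of 10-30% and on independent normal covariates. The covariate count and the sample size come from the protocol.

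For time to healing, the delay is about 4 to 9 weeks under the assumed healing times, and only if the first healed visit is used as the date.

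Severity is minor. Only secondary outcomes of a descriptive case series are affected. The planned frequencies are sound, and this point does not touch the Quick-DASH result.

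**What to change.** 1. Limit the "similar models" sentence to the continuous outcomes.
2. Report complications and secondary interventions as counts with exact 95% confidence intervals and no multivariable model. At most, allow a Firth logistic model with one covariate, labelled exploratory.
3. Report healing as the cumulative proportion healed by each scheduled visit, using an interval-censored estimate that keeps unhealed patients as censored, in place of a mean or median of visit dates.

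The cost is a change of analysis wording; the data are already being collected. The downside is that the event outcomes will have no covariate-adjusted associations.
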